**LIST OF ABBREVIATIONS AND RELEVANT DEFINITIONS**

|         |                                                                                                                                                                                   |
|---------|-----------------------------------------------------------------------------------------------------------------------------------------------------------------------------------|
| ABR     | General Assessment and Registration form, the application form that is required for submission to the accredited Ethics Committee (in Dutch: Algemene Beoordeling en Registratie) |
| AEE     | Activity-induced energy expenditure                                                                                                                                               |
| AR      | Adverse Reaction                                                                                                                                                                  |
| BMI     | Body mass index                                                                                                                                                                   |
| CA      | Competent Authority                                                                                                                                                               |
| CAPS    | Capsaicin                                                                                                                                                                         |
| CCMO    | Central Committee on Research Involving Human Subjects (in Dutch: Centrale Commissie Mensgebonden Onderzoek)                                                                      |
| CV      | Curriculum Vitae                                                                                                                                                                  |
| DHC     | Dihydrocapsaicin                                                                                                                                                                  |
| DIT     | Diet-induced thermogenesis                                                                                                                                                        |
| DSMB    | Data Safety Monitoring Board                                                                                                                                                      |
| EE      | Energy expenditure                                                                                                                                                                |
| En%     | Energy percent                                                                                                                                                                    |
| EU      | European Union                                                                                                                                                                    |
| EudraCT | European drug regulatory affairs Clinical Trials                                                                                                                                  |
| FFM     | Fat free mass                                                                                                                                                                     |
| FM      | Fat mass                                                                                                                                                                          |
| FMI     | Fat mass index                                                                                                                                                                    |
| GCP     | Good Clinical Practice                                                                                                                                                            |
| IB      | Investigator's Brochure                                                                                                                                                           |
| IC      | Informed Consent                                                                                                                                                                  |
| IMP     | Investigational Medicinal Product                                                                                                                                                 |
| IMPD    | Investigational Medicinal Product Dossier                                                                                                                                         |
| METC    | Medical Research Ethics Committee (MREC) (in Dutch: Medisch Ethische Toetsing Commissie)                                                                                          |
| NDC     | Nordihydrocapsaicin                                                                                                                                                               |
| PA      | Physical activity                                                                                                                                                                 |
| POMS    | Profile of Mood States                                                                                                                                                            |
| RMR     | Resting metabolic rate                                                                                                                                                            |
| RQ      | Respiratory quotient                                                                                                                                                              |
| (S)AE   | (Serious) Adverse Event                                                                                                                                                           |

|         |                                                                                                                                                                                                                                                                                                                            |
|---------|----------------------------------------------------------------------------------------------------------------------------------------------------------------------------------------------------------------------------------------------------------------------------------------------------------------------------|
| SEM     | Standard error of the mean                                                                                                                                                                                                                                                                                                 |
| SHU     | Scoville heat units                                                                                                                                                                                                                                                                                                        |
| SMR     | Sleeping metabolic rate                                                                                                                                                                                                                                                                                                    |
| SO      | Substrate oxidation                                                                                                                                                                                                                                                                                                        |
| SPC     | Summary of Product Characteristics (in Dutch: officiële productinformatie IB1-tekst)                                                                                                                                                                                                                                       |
| Sponsor | The party that commissions the organisation or performance of the research, for example a pharmaceutical company, academic hospital, scientific organisation or investigator. A party that provides funding for a study but does not commission it is not regarded as the sponsor, but referred to as a subsidising party. |
| STAI    | State-trait anxiety inventory                                                                                                                                                                                                                                                                                              |
| SUSAR   | Suspected Unexpected Serious Adverse Reaction                                                                                                                                                                                                                                                                              |
| TBW     | Total body water                                                                                                                                                                                                                                                                                                           |
| VAS     | Visual analogue scale                                                                                                                                                                                                                                                                                                      |
| WHR     | Waist-to-hip ratio                                                                                                                                                                                                                                                                                                         |
| Wbp     | Personal Data Protection Act (in Dutch: Wet bescherming persoonsgegevens)                                                                                                                                                                                                                                                  |
| WMO     | Medical Research Involving Human Subjects Act (in Dutch: Wet Medisch-wetenschappelijk Onderzoek met Mensen)                                                                                                                                                                                                                |

## SUMMARY

**Rationale:** Red pepper might prevent reduction of energy expenditure and elevation of hunger as a result of energy intake restriction.

**Objective:** To investigate the acute effects of capsaicin on energy expenditure, substrate oxidation, appetite profile and *ad libitum* energy intake during negative energy balance.

**Study design:** The study will be conducted in a crossover design with four randomly sequenced conditions. Energy expenditure and substrate oxidation will be continuously monitored for 36h. Appetite profile will be measured hourly. *Ad libitum* energy intake will be measured during the last meal.

**Study population:** Sixteen healthy subjects (8 males and 8 females) with BMI between 20-30 kg/m^2 and aged between 18-50 years will be included in the study. All subjects will be non-smoking, weight stable, dietary unrestrained, and at most moderate alcohol and caffeine consumers. Subject will be free of medication except for oral contraceptives use in women.

**Intervention:** Subjects will stay for each of the four conditions in a respiration chamber for 36h, twice receiving an energy-balanced (100 En%) diet and twice an energy-restricted (75 En%) diet, both with and without added capsaicin (100%control, 75%control, 100%CAPS, 75%CAPS). An *ad libitum* meal will be served at the end of the second day.

**Main study parameters/endpoints:** Energy expenditure, substrate oxidation, appetite profile and *ad libitum* energy intake.

**Nature and extent of the burden and risks associated with participation:**

The study does not include any major risk for the subjects. Anthropometric and body composition measurements, performed during the screening, will not be invasive for the subjects. Deuterium dilution has been shown to be a safe method for determining total body water. Furthermore, the registration of oxygen consumption and carbon dioxide production in the respiration chamber will be performed during an unconscious process. The air in the chamber is continuously regulated.

Urine sampling will be done in urine bottles added with diluted HCl, which might pose a risk for the subjects. However, subjects will be carefully instructed how to handle the bottles to reduce these risks.

Additionally, there are no risks for the subject in consuming any of the provided meals, because people with certain food allergies are excluded for participation and all meals are composed of regular food items available in normal Dutch supermarkets. The addition of capsaicin to the meals will not form any health risk. Capsaicin is a natural product, which is safe in the given dose that will not exceed the maximum recommended daily dose.

**Benefit:** This study does not have any benefits for the subjects themselves, but will give possible new knowledge for the treatment of obesity.

## 1. INTRODUCTION AND RATIONALE

Obesity is associated with an increased risk for chronic diseases including type 2 diabetes, cancer, and cardiovascular diseases (1). The development of obesity results from a chronic energy imbalance, with energy intake exceeding energy expenditure. Both decreasing energy intake and increasing energy expenditure may result in weight loss. Modest weight loss (5–10% of body weight) is associated with clinical improvements in insulin sensitivity and fasting glucose levels, thereby reducing the risk for the development of type 2 diabetes (2). Furthermore, reductions in dyslipidemia and hypertension as a result of weight loss reduce the risks for cardiovascular diseases (3).

Under normal circumstances, body weight is very tightly regulated. After a period of energy restriction and weight loss, the body will respond using several mechanisms as increasing feelings of hunger and decreasing energy expenditure to regain its initial body weight (4). These counteractive mechanisms make adherence to weight-loss diets difficult and uncomfortable (5). Therefore, it is of importance to design weight-loss diets that tackle the undesirable physiological responses of the body. Several food components have been studied for their effect on appetite related feelings and thermogenesis. For instance capsaicin, the pungent principle of red pepper, has been reported to increase energy expenditure and diet-induced thermogenesis and to imply a shift in substrate oxidation from carbohydrate to fat oxidation (6-11). For weight-reduction strategies it is necessary to know whether these effects of capsaicin are still present during a moderate energy deficit. In short-term human studies, addition of red pepper to experimental meals significantly increased diet-induced thermogenesis and lipid oxidation (6, 11). In Caucasian male subjects, using a respiration chamber design, red pepper and caffeine consumption was observed to significantly increase 24h energy expenditure (7). Furthermore, in a long-term study, a relatively more sustained fat oxidation in the capsaicin group was observed compared with the placebo group (8). The increase in diet-induced thermogenesis is probably caused by enhancing catecholamine secretion from the adrenal medulla as observed in rats, mainly through activation of the central nervous system (12-17). This is probably based on  $\beta$ -adrenergic stimulation, since both animal and human studies showed that the increase in thermogenesis is abolished after administration of  $\beta$ -adrenergic blockers such as propranolol. Furthermore, the presence of a functional capsaicin-like vanilloid receptor, the Transient Receptor Potential Vanilloid receptor 1 (TRPV1), has been observed in the rats. This vanilloid receptor is expressed in sensory neurons, the brain and various non-neuronal tissues and might mediate oxygen uptake, and thus thermogenesis (12-17).

Capsaicin has also been reported to increase satiety and to decrease appetite and *ad libitum* food intake (7, 10, 18-20). The addition of capsaicin to a test meal was found to reduce food consumption during a subsequent *ad libitum* meal. A significant decrease in energy intake

was observed after offering capsaicin as an appetizer (18). Red pepper supplementation combined with caffeine significantly reduced the daily *ad libitum* energy intake (7). In a study of [name] et al., average daily energy intake over two days was reduced when capsaicin was offered in tomato juice or in capsules, compared to the control condition (19). Reinbach et al. found that one-day exposure to capsaicin increased satiety during negative energy balance (21). It is necessary to know whether during negative energy balance energy expenditure and fat oxidation are still stimulated more after capsaicin supplementation than in a control situation in the same negative energy balance. The present study aims to investigate the 36h effects of capsaicin on energy expenditure, substrate oxidation and appetite profile, and *ad libitum* energy intake during 25% negative energy balance. It will be investigated whether the 36h effects of capsaicin in 25% negative energy balance prevent the effects of the negative energy balance on energy expenditure, substrate oxidation, appetite profile and *ad libitum* energy intake compared to 100% energy intake without capsaicin.

## 2. OBJECTIVES

The primary objective of this study is to investigate whether the 36h effects of capsaicin in 25% negative energy balance prevent the effects of the negative energy balance on energy expenditure, substrate oxidation, appetite profile and *ad libitum* energy intake compared to 100% energy intake without capsaicin (75%CAPS vs. 100%Control).

Because of the cross-over design of this study, it needs to be assessed whether, and to which extend, 75% energy intake without capsaicin decreases energy expenditure and satiety compared to 100% energy intake without capsaicin (75%Control vs. 100%Control). In this way, this study will assess the effectiveness of capsaicin as bioactive ingredient during negative energy balance.

The primary objective implies that 100% energy intake with capsaicin increases energy expenditure, fat oxidation and satiety compared to 100% energy intake without capsaicin (100%CAPS vs. 100%Control). Previous studies have shown comparable effects of capsaicin supplementation, but different subject groups and supplementation protocols were used. This study needs to determine whether capsaicin supplementation is effective over 36h in this specific study setting.

Negative energy balance causes a shift in substrate oxidation, leading to a higher fat oxidation compared to energy balance conditions. This study will test the hypothesis that the increase in fat oxidation will be larger in the 75% energy intake with capsaicin condition compared with 75% energy intake without capsaicin condition (75%CAPS vs. 75%Control).

Four conditions will be applied in order to completely answer the research questions:

- 100% energy balance without capsaicin (100%Control)
- 75% energy balance without capsaicin (75%Control)
- 100% energy balance with capsaicin (100%CAPS)
- 75% energy balance with capsaicin (75%CAPS)

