### 4.4. Sample size calculation

The primary endpoint of this study is the change in 36h energy expenditure.

For the sample size calculation the following formula was used:

$$N = 2 + (Z_{1-\beta} + Z_{1-\alpha/2})^2 \times \sigma^2 / (\mu_{75\%CAPS} - \mu_{75\%CONTROL})^2$$

Herein the  $\beta$  was set at 0.10, which results from a power of 0.9. Consequently,  $Z_{0.9} = 1.28$ . For the  $\alpha$  a value of 0.05 was chosen, which resulted in  $Z_{0.975} = 1.96$ .

It is hypothesized that the 25 En% restriction CAPS diet will show a relatively larger 36h energy expenditure compared with the 25 En% restriction control diet. A study by Yoshioka et al. showed that a combination of red pepper and caffeine significantly increased 24h energy expenditure compared to a control condition ( $10190 \pm 1550$  vs.  $9870 \pm 1490$ ,  $p < .05$ ) (7). This corresponds to an increase in 24h energy expenditure of 320 kJ/24h. Therefore, the smallest change in 36h energy expenditure ( $\mu_{75\%CAPS} - \mu_{75\%CONTROL}$ ) was set at  $1.5 \times 320 = 480$  kJ/36h. The standard deviation was set at 550 kJ/36h, based on several studies performed in the same setting to measure energy expenditure with a respiration chamber as will be used in the current study (25, 26).

The calculated sample size will be:

$$N = 2 + (1.28 + 1.96)^2 \times 550^2 / 480^2 = 14 \text{ subjects}$$

Taking a drop-out of 10% into account, 16 subjects will be included in the experiment.

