### **8.2. Univariate analysis**

The Statistical Package for the Social Sciences (SPSS) will be used to perform univariate analyses. ANOVA repeated measures will be performed to determine possible differences in energy expenditure and its components, substrate oxidation, *ad libitum* energy intake, energy and macronutrient balance, appetite profiles and mood scores between the four conditions. Multiple linear regression analyses will be performed to determine the independent contribution of gender, age, and factors describing body composition and body fat distribution on the dependent variables. All statistical tests will be two-sided and differences will be considered statistical significant if  $p < .05$ .

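### The primary objective (75%CAPS vs 100%Control, prevention) is not the contrast that was sized (75%CAPS minus 75%Control), and the planned difference tests cannot by themselves show prevention

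*Protocol*

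**What the plan says.** Three parts of the protocol bear on this.

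- **Section 2 (Objectives).** The primary objective asks "whether the 36h effects of capsaicin in 25% negative energy balance prevent the effects of the negative energy balance on energy expenditure" and the other outcomes, "compared to 100% energy intake without capsaicin (75%CAPS vs. 100%Control"). The section then says that the effect of restriction itself (75%Control vs 100%Control) needs to be assessed. It lists 75%CAPS vs 75%Control last, as a hypothesis about fat oxidation.
- **Section 4.4 (Sample size calculation).** "The primary endpoint of this study is the change in 36h energy expenditure". The hypothesis used for sizing is that "the 25 En% restriction CAPS diet will show a relatively larger 36h energy expenditure compared with the 25 En% restriction control diet". The difference for that pair "was set at $1.5 \times 320 = 480$ kJ/36h", and "The standard deviation was set at 550 kJ/36h". The result is 14 subjects, raised to 16 for 10% drop-out.
- **Section 8.2 (Univariate analysis).** Repeated-measures ANOVA looks for differences between the four conditions. "All statistical tests will be two-sided and differences will be considered statistical significant" at p < .05.

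No section gives an equivalence or non-inferiority margin, an expected difference for 75%CAPS vs 100%Control, or an expected loss for 75%Control vs 100%Control.

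**The concern.** Full prevention predicts that energy expenditure under 75%CAPS is no lower than under 100%Control, so the expected difference on the primary contrast is zero or above. A two-sided difference test with no margin cannot establish a zero difference; it can only fail to find one. A noisier measurement or fewer completers makes that failure more likely, so imprecision works in favour of the claim.

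The 90% power protects against missing a 480 kJ gain of 75%CAPS over 75%Control. That is a superiority question, and section 2 does not call it primary. A reader of the final report could take the trial as powered for its primary objective when it is powered for a different comparison. The trial could also be read as showing that capsaicin prevents the fall in expenditure when a sizeable part of the fall remains.

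**Working it through.** **Inputs from section 4.4.** Difference 480 kJ/36h for 75%CAPS minus 75%Control; SD 550 kJ/36h; z-values 1.28 and 1.96; 14 subjects before drop-out, 16 after.

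**Assumption.** Section 4.4 does not say what kind of SD 550 is. It is taken here as the SD of within-subject differences, which fits the use of a single-sample formula, and the same SD is used for 75%CAPS vs 100%Control. The alternative is shown at the end.

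**1. The plan's own figure.** (1.28 + 1.96)² × 550² / 480² = 10.4976 × 1.3129 = 13.78, rounded up to 14. Then 14 / 0.90 = 15.6, rounded up to 16. The figure is reproduced, and it concerns 75%CAPS minus 75%Control only. (The printed formula has a leading 2 +, which would give 15.78. That is a separate matter and does not affect this point.)

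**2. Chance that a real remaining deficit is non-significant on the primary contrast.** Paired t-test, two-sided .05, n − 1 degrees of freedom, noncentrality = deficit / (550/√n). The standard error is 550/√14 = 147.0 kJ or 550/√16 = 137.5 kJ.

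| True deficit, 75%CAPS below 100%Control | P(p ≥ .05), 14 completers | P(p ≥ .05), 16 completers |
|---|---|---|
| 150 kJ | 84% | 82% |
| 240 kJ (half of 480) | 67% | 63% |
| 320 kJ | 48% | 41% |
| 480 kJ | 14.5% | 10% |

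**3. Precision of the primary contrast.** The 95% CI half-width is t × standard error.
- 14 completers: 2.160 × 147.0 = 318 kJ, and 318/480 = 0.66.
- 16 completers: 2.131 × 137.5 = 293 kJ, and 293/480 = 0.61.

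An observed difference of exactly zero would thus leave deficits of about 300 kJ within the interval.

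**4. Would adding a margin be enough?** Non-inferiority at one-sided .025, true difference zero, 14 completers, SD 550: power is 86% for a margin of 480 kJ, 52% for 320 kJ and 33% for 240 kJ. For 90% power, 480 kJ needs 16 completers, 320 kJ needs 34 and 240 kJ needs 58. These margins are illustrations, since the protocol gives none. Only a margin as large as the whole design effect suits this sample size.

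**5. If 550 is a per-condition SD with no within-subject correlation.** The SD of differences is 550 × √2 = 778. With 14 completers a 240 kJ deficit is then non-significant 81% of the time and a 480 kJ deficit 43% of the time, and the half-width is 449 kJ.

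**The case against.** There are several fair points on the plan's side.

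- **No rule equates non-significance with prevention.** A reader might infer that the primary objective can only be met by p ≥ .05. The protocol does not say so, and significantly higher expenditure under 75%CAPS than under 100%Control would also meet it. That route requires capsaicin to more than offset the restriction. What stands is that full prevention without such an excess would, in practice, be inferred from a null result.
- **The restriction effect is not ignored.** A reader might infer that the prevention claim is detached from any check that restriction lowers expenditure. Section 2 says directly after the primary objective that this must be assessed, and ties it to judging capsaicin's effectiveness. The link is written, but it is not a condition on the claim.
- **The sized contrast is not foreign to the trial.** Section 1 states a need to know whether capsaicin still raises energy expenditure relative to a control in the same negative energy balance. The fault is in which contrast is called primary.
- **The four conditions can be read together.** Requiring a shown restriction loss, and a gain of 75%CAPS over 75%Control, would greatly reduce false claims. The protocol permits that reading but does not require it.
- **A statistical analysis plan might add a margin.** It might, but that would not move the stated power to the named primary contrast, and step 4 of the working shows that a tight margin would be underpowered.

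A reader may also want the rate of false prevention claims if capsaicin does nothing. That depends on the restriction loss, which the protocol does not quantify. An assumed loss of 413 kJ (thermic effect 10% of intake, the protocol's example man) gives 20% non-significant with 16 completers, and 71% if capsaicin restores half. Thermic effects of 5% to 12% move the first figure from 71% to 8%. These are illustrations only, and the conclusion does not use them.

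**Conclusion.** The point holds as a mismatch between objective, sizing and test. Section 2 names 75%CAPS vs 100%Control as primary, section 4.4 gives the 90% power to 75%CAPS minus 75%Control, and section 8.2 offers only difference tests without a margin. A non-significant result on the named primary contrast would be weak evidence of prevention: half of the design effect could remain as a deficit and still be non-significant about two times in three.

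The mismatch rests on the text alone. The probabilities rest on 550 kJ being the SD of paired differences and applying to this contrast; a larger SD makes them worse. The documents do not support saying that the protocol adopts non-significance as its success rule, or that any particular false-claim rate has been established.

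**What to change.** Change the wording in sections 2, 4.4 and 8.2:

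1. Make 75%CAPS minus 75%Control on 36h energy expenditure the primary contrast, tested for superiority, as already sized.
2. Make 75%CAPS vs 100%Control secondary. Report it as an estimate with 95% confidence interval next to the 75%Control vs 100%Control estimate.
3. Interpret it as prevention only if the 75%Control vs 100%Control loss is demonstrated.
4. State that a non-significant 75%CAPS vs 100%Control difference is not evidence of prevention.

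The cost is wording: no extra subjects or measurements are needed for the sized contrast. The downside is that full prevention becomes harder to claim. A formal non-inferiority claim is not recommended at this size, because a tight margin would be underpowered (33% for 240 kJ with 14 completers) and the protocol gives no expected restriction loss from which to derive one. If the sponsor wants to keep prevention as the primary claim, a margin must be justified beforehand and the trial resized.
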